### Data collection

Data collection commenced in February 2012 following completion of piloting. Whilst the challenges of delivering online surveys are well documented [28], it was decided to be the most feasible and practical first method of delivery with subsequent delivery of a postal version to non-respondents and persons who do not have a working email address or access to a computer.

### Sample size

Given that the specific questions developed for this study to measure confidence to cook (cooking self-efficacy) have not been previously employed, a precise sample size calculation for this primary outcome could not be calculated given the absence of a priori baseline measures, measures of effect size and measures of variance (standard deviation).

Sample size calculations around the second primary outcome of a change in vegetable intake between the two groups assumed the use of a split-plot anova and F test for interaction given the wait list design. The literature does not provide clear guidance with regards to an expected effect size for a program of this nature [29,30]. However, as there is some evidence from Wrieden et al that an effect size of one serve per day may be too large for a program of this nature [20], sample size calculations are based on an effect size range likely to be achieved [29,30]. For an effect size of 0.5 serves a day, starting from a mean daily consumption at baseline of 2.5 serves per day [13,23], 250 subjects per group will be required at 80% power (0.05 significance). In the event that accrual is slower than expected, recruiting at least 140 participants will give 80% power for an effect size of 0.7 serves a day. There will be no analysis of the data before accrual has closed.

### Data analysis

Demographic and baseline characteristics will be summarised for both intervention and control groups using standard summary statistics (mean and standard deviation) and non-parametric statistics (medians and inter-quartile ranges) where applicable. Frequencies and percentages will be reported for categorical variables. The magnitude of change both within and between intervention and control groups for T1, T2 and T3 time-points will be assessed. For continuous data, such as fruit and vegetable intake, two sample t tests will be employed to compare means between intervention and control groups at each time point and paired t tests for within group comparisons. A split-plot in time Anova will be used as the basis for these t-tests. For categorical data, frequencies will be reported for intervention and control groups and chi squared analysis will provide between group comparison results. Regression analysis will be conducted to determine the potential contribution of specific demographic factors on the outcome variables of interest. All data analysis will be performed using STATA S.E. 12.0 statistical software.

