**Methods/Design:**

A mixed methods study design is proposed. Given the programmatic implementation of JMoF in Ipswich, the quantitative study is a non-randomised, pre-post design comparing participants undergoing the program with a wait-list control group. There will be two primary outcome measures: (i) change in cooking confidence (self-efficacy) and (ii) change in self-reported mean vegetable intake (serves per day). Secondary outcome measures will include change in individual cooking and eating behaviours and psycho-social measures such as social connectedness and self-esteem. Repeated measures will be collected at baseline, program completion (10 weeks) and 6 months follow up from program completion. A sample of 250 participants per group will be recruited for the evaluation to detect a mean change of 0.5 serves a day of vegetables at 80% power (0.5% significance level). Data analysis will assess the magnitude of change of these variables both within and between groups and use sub group analysis to explore the relationships between socio-demographic characteristics and outcomes.

The qualitative study will be a longitudinal design consisting of semi-structured interviews with approximately 10-15 participants conducted at successive time points. An inductive thematic analysis will be conducted to explore social, attitudinal and behavioural changes experienced by program participants.

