### Quantitative study

### Research questions

The quantitative component of the evaluation will answer the following research questions:

1. Does the JMoF program increase participants’ skills, knowledge, attitudes, enjoyment and satisfaction of cooking and cooking confidence (self-efficacy)?

2. Does the JMoF program result in broader positive outcomes for participants in terms of behaviour change to a healthier diet, more affordable healthy meals, improved self-esteem and social connectedness?

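### The named change tests use only people with both surveys, so follow-up loss that depends on intake and differs between arms can bias the program effect

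*Protocol article*

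**What the plan says.** In the protocol article, the Data analysis section of the quantitative study names the methods for continuous outcomes such as vegetable intake: "two sample t tests will be employed to compare means between intervention and control groups at each time point and paired t tests", the latter to assess change inside each group. It adds: "A split-plot in time Anova will be used as the basis for these t-tests". The Sample size section rests on the same model; the calculation for vegetable intake "assumed the use of a split-plot anova and F test for interaction given the wait list design".

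The planning figures are in the same section: "For an effect size of 0.5 serves a day, starting from a mean daily consumption at baseline of 2.5 serves per day", and "250 subjects per group will be required at 80% power (0.05 significance" level). The second research question asks about participants: "Does the JMoF program result in broader positive outcomes for participants in terms of behaviour change to a healthier diet".

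Intervention participants are surveyed at T1, T2 (10 weeks) and T3 (six months after completion), controls at T1 and T2 only. Surveys are self-administered online, with a postal version for non-respondents.

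**The concern.** A paired t test needs both measurements. With two time points, the split-plot group-by-time test is equivalent to a t test on change scores, so as usually fitted it takes nothing from a person with a baseline survey alone. The T2 and T3 comparisons use whoever answered that survey, but the T1 comparison uses everyone with a baseline. The named tests can therefore describe different sets of people.

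This matters if loss is related to intake and is not alike in the two arms. The design makes that plausible without showing it: the intervention arm's T2 survey follows a 10-week course paid for by class, whereas the controls' T2 survey falls at program entry. If intervention non-responders are mainly people with low baseline intake, those retained start higher and tend to regress, so the change analysis comes out too low. They also eat more at T2 regardless of the program, so the T2 t test comes out too high. The plan would then give two different answers on a primary outcome. The intervention arm's own T1-T3 change is exposed in the same way, over the longest interval.

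**Working it through.** **The plan's figures.** Effect 0.5 serves, 250 per group, 80% power, 0.05 (taken as two-sided). No SD is given. The implied SD of change is 0.5 × √(250/2) / (1.960 + 0.842) = 1.995, about 2.0 serves. The abstract prints the level differently, "0.5 serves a day of vegetables at 80% power (0.5% significance level"); the Sample size section's 0.05 is used here. The hand calculation below is in serves and does not need the SD, which serves only to judge whether a gap is large.

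**Assumptions, because the article gives no values.** Loss depends on baseline intake only; equal variance at T1 and T2; T1-T2 correlation ρ = 0.5, so the SD of intake is also 1.995 / √(2 × 0.5) = 1.995. Let m be the share lost in an arm and G the baseline gap between responders and non-responders. A gap of 0.6 serves is about 0.3 SD.

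**Formulas.** Retained people in an arm start m × G above that arm's full baseline mean. Write D = m_I G_I − m_C G_C. Then:

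- bias of the change (interaction) analysis = −(1 − ρ) × D
- bias of the T2 two-sample comparison = +ρ × D

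**Results for a true effect of 0.50 (ρ = 0.5).**

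| Intervention loss, gap | Control loss, gap | D | Change analysis | T2 t test |
|---|---|---|---|---|
| 20%, 0.6 | 10%, 0 | 0.12 | 0.44 (−12%) | 0.56 (+12%) |
| 20%, 1.0 | 10%, 0 | 0.20 | 0.40 (−20%) | 0.60 (+20%) |
| 30%, 0.6 | 10%, 0 | 0.18 | 0.41 (−18%) | 0.59 (+18%) |
| 20%, 0.6 | 10%, 0.6 | 0.06 | 0.47 (−6%) | 0.53 (+6%) |
| 30%, 0.6 | 10%, 0.6 | 0.12 | 0.44 (−12%) | 0.56 (+12%) |
| 20%, 0.6 | 20%, 0.6 | 0 | 0.50 (0%) | 0.50 (0%) |

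Large-sample simulation agrees to about 0.01; the first row, for example, gives 0.444 and 0.550.

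**Sensitivity to ρ.** At ρ = 0.7 with the SD of change held at 1.995, the SD of intake is 1.995 / √0.6 = 2.58, and 0.3 SD is a gap of 0.77. With 20% intervention loss and random control loss, D = 0.155. The change analysis is then biased by −0.3 × 0.155 = −0.046 and the T2 test by +0.7 × 0.155 = +0.108. Simulation gives 0.456 (−9%) and 0.606 (+21%).

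**Stronger baseline dependence.** With about 30% loss in each arm, and intervention loss alone tied steeply to baseline intake, the simulated change estimate falls to 0.25-0.37 (−50% to −27%).

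**What a likelihood model does.** Using all baselines, it returned 0.50 wherever loss depended on baseline only. That is expected by construction, since this is the case it is built for. When intervention loss depended on the change itself, the change analysis gave 0.68-0.86 and the likelihood model still gave 0.64-0.76. When the same change-related mechanism acted in both arms, the change analysis gave 0.47-0.48 (−7% to −4%).

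**Non-responders who gain nothing.** If a share d of the intervention arm is lost and gained nothing, the responder-only effect is inflated by d / (1 − d): 0.10/0.90 = 11% at 10% loss, and 0.20/0.80 = 25% at 20% loss.

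**The case against.** The strongest reply is that the size rests on assumptions. The article reports no attrition, no SD and no link between response and intake. Both arms receive the same online-then-postal survey, and the only survey incentive applies at T3. With the same intake-related mechanism in both arms and 20% against 10% loss, the bias is about 6%; with identical loss it is nil. This stands. A reader might infer that the plan will shift the effect by 10% or more, and the documents do not support that.

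Second, a split-plot model can be fitted by likelihood using every record, and the article does not state the estimator. That is true of the ANOVA, but not of the paired and two-sample t tests that are named. If a likelihood fit is intended, the change amounts to saying so.

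Third, missing-data handling is commonly left to a full protocol or SAP, and the article does describe follow-up of non-responders and several ways to complete the survey. A reader might conclude that non-response was overlooked. That does not follow, and the absence of a missing-data section is not the point here. These are collection measures, however, and they do not alter which people the named tests use.

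Fourth, the mixed model does not help when loss depends on unobserved change, which is what stopping a course might produce. This also stands, and is why a sensitivity analysis is needed.

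**Conclusion.** The point holds in conditional form. The paired tests and the split-plot interaction in effect restrict the change analysis to people with both surveys, and the T2 and T3 t tests restrict to that survey's responders. It would be too broad to infer that every named test drops baseline-only participants, because the T1 test keeps them.

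Bias in the between-group effect needs loss that depends on intake and whose rate or mechanism differs between arms. Under 20-30% intervention loss against 10% control loss, ρ = 0.5 and gaps of 0.6 to 1.0 serve, it is about 6% to 20% of a 0.5-serve effect. The two named between-group analyses err in opposite directions when loss falls on low baseline intake. That direction is specific to this mechanism: if non-responders simply gained less, the change analysis would be too high. Nothing in the documents fixes where in this range the trial will fall. The change is nevertheless worth making, because the better analysis uses data already collected and needs a weaker assumption about loss.

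**What to change.** In the Data analysis section, make the primary analysis of the continuous outcomes a likelihood-based linear mixed model for repeated measures with group, time and group-by-time:

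- Include everyone with at least one survey.
- Leave baseline means free by group, since allocation is not randomised.
- Report the group-by-time contrast at T2 as the program effect.
- Take the intervention arm's T1-T3 change from the same model; controls have no T3 survey.

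Add one sensitivity analysis that sets non-responders' change to zero, because the model removes bias only when loss is explained by the observed surveys.

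The cost is a wording change and slightly more analysis work in the software already named, with no extra data or participants. The sensitivity analysis may give a less favourable figure. The Sample size section rules out any analysis before accrual closes, so the change can be made without sight of results.

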### Study design

A quasi-experimental pre-post design will consist of an intervention group of participants undergoing the JMoF program and a control group comprising of participants from the program waitlist who are waiting for at least 10 weeks until program entry. Recruitment to each group will be based on program start date and will not be subject to randomisation. Randomisation was not possible as it would not allow participants any choice as to when and with whom they participated in the program – which are important aspects of the JMoF program design [20].

Intervention participants will be surveyed at three time-points: program commencement, program completion (10 weeks) and at six months post program completion. Controls drawn from the waitlist will be surveyed at two time-points: 10 weeks prior to program commencement and on completion of their 10 weeks on the waitlist (which will correspond to their program entry). A time-three measurement will not be obtained from controls as it was considered neither feasible nor acceptable for the waitlist controls to have to wait a further six months before entering the program (equivalent to the intervention follow-up period); this potentially would lead to a high drop-out rate both from the evaluation and the program itself. However, for one of the primary outcome measures, vegetable intake, Queensland state-wide monitoring data will be used as a proxy time-three measure for the control group.

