### Recruitment

All participants registered on the JMoF Australia waitlist database, aged 18 years or over, and who had received a confirmed start date for the program, will be eligible to participate in the quantitative component of the evaluation. Whilst the program is open to all members of the Ipswich community over the age of 12 years, the evaluation will target the adult population only as other cooking skills programs exist within the Greater Ipswich region that are specifically targeting children and adolescents in educational settings.

All participants will be required to consent prior to participation in the evaluation. A link to the questionnaire will be embedded within an email generated by the JMoF program database, inviting program participants to participate in the evaluation questionnaire.

Recruitment to both groups will be based on confirmed program start dates. As control participants are required to be on the program waitlist for 10 weeks and because the JMoF waitlist is sufficiently large to enable this to occur naturally, participants that are allocated a start date longer than 10 weeks ahead, will be automatically made a control, whilst persons commencing the program within 10 weeks will be assigned to the intervention group. Computer programmed “rules” in the JMoF participant database have been created to automate this process.

To show appreciation for participation, those intervention participants who complete the third and final questionnaire at six months post completion of the program will be sent a $20 “Good Guys” store charge card redeemable at any Good Guys store (white goods retailer) across Australia.

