## Discussion

The evaluation of the JMoF program will contribute to the growing body of literature on the effectiveness of community-based cooking skills programs. It will employ a mixed methodology to draw on the strengths of both quantitative and qualitative study design to best capture and measure experiences, impacts and outcomes of cooking skills programs. The methods described herein will inform the research community about program outcomes and facilitate comparisons of results with other cooking skills programs conducted in comparable populations.

This study will also provide insights into practical considerations required when designing program evaluations in community settings. These include factors such as recruitment of a comparison group, minimisation of participant data collection burden, and the suitability and feasibility of selected data collection modes, which must be considered without compromising study design or program integrity.

There are both strengths and limitations to the evaluation design. Mixed methods studies as a paradigm can risk compromising methodological rigour if integration occurs at point of data collection and/or analysis and potentially undermines paradigm and process considerations [18,19]. This is not an issue in the current evaluation with integration only occurring in relation to sample identification and final integration of findings.

Whilst it is acknowledged that the use of a non-randomised quasi-experimental design makes the quantitative study vulnerable to sampling bias, practical limitations prevented the application of a randomised design. Despite this potential bias, the use of a waitlist control and pre and post measures support attribution of any changes to the program.

Potential selection bias associated with choice to participate or not in the quantitative study may also occur. However various methods were employed in an attempt to address this issue: providing participants with multiple options for survey completion, follow up of non-responders and the use of incentives.

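### Groups formed by start date are compared with unadjusted tests, and the group-by-time contrast that sized the trial is not named as the test of the program effect

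*Protocol article*

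**What the plan says.** **Group formation.** The Study design section of the quantitative study states: "Recruitment to each group will be based on program start date and will not be subject to randomisation". Randomisation was ruled out because "it would not allow participants any choice as to when and with whom they participated in the program". The Recruitment section gives the working rule: "participants that are allocated a start date longer than 10 weeks ahead, will be automatically made a control". Those who start within 10 weeks form the intervention group.

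**Sample size.** The calculation for vegetable intake "assumed the use of a split-plot anova and F test for interaction given the wait list design". It gives 250 per group for a 0.5-serve effect at 80% power and 0.05 significance.

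**Analysis.** The quantitative Data analysis section says that change within and between groups will be assessed. It then names the tests for continuous outcomes: "two sample t tests will be employed to compare means between intervention and control groups at each time point", with paired t tests within groups. It adds: "A split-plot in time Anova will be used as the basis for these t-tests". Categorical outcomes get chi-squared comparisons. The only mention of covariates is: "Regression analysis will be conducted to determine the potential contribution of specific demographic factors on the outcome variables of interest".

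**Interpretation.** The Discussion concedes that the non-randomised design is open to sampling bias, then states that "the use of a waitlist control and pre and post measures support attribution of any changes to the program".

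**The concern.** When start date decides the group, people who start soon may differ from those who start later in motivation, availability or household circumstances. The timing of baseline differs too: intervention participants are first surveyed as they begin the program, controls 10 weeks before they begin. Baseline differences, and differences in how the groups would have changed anyway, are therefore plausible, although the article gives no figure for either.

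Two separate problems follow.

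- **Baseline gap.** A comparison of means at 10 weeks counts any gap that was already there at baseline as program effect.
- **Confounded change.** A comparison of changes removes a constant gap. It does not deal with factors that are linked to start date and also influence change. Only adjustment for measured factors addresses these, and no adjusted program effect is stated.

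Both primary outcomes, cooking confidence and vegetable intake, depend on this contrast, and so does the Discussion's statement on attribution.

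**Working it through.** **Inputs from the article.** 250 per group, 0.5 serves per day, 80% power, significance 0.05 (Sample size). A two-sided test is assumed. The article gives no SD, no within-person correlation and no expected baseline gap, so these are assumptions shown as ranges.

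**Step 1: the plan's own figure.** Without an SD, 250 cannot be reproduced forward, only back-solved. With two time points, the split-plot interaction test is a two-sample t test on change, so

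SD of change = 0.5 × √(250/2) / (1.960 + 0.842) = 5.590 / 2.802 = 1.995 serves.

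**Step 2: the t test at 10 weeks, no program effect, constant baseline gap g.**

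Standard error = SD × √(2/250); k = g / standard error; rejection rate = 1 − Φ(1.96 − k) + Φ(−1.96 − k).

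| Gap (serves) | SD 2.0: k | Rejection | SD 1.5: k | Rejection |
|---|---|---|---|---|
| 0.10 | 0.56 | 8.6% | 0.75 | 11.6% |
| 0.25 | 1.40 | 28.7% | 1.86 | 46.2% |

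The nominal rate is 5%, and the whole gap appears as program effect.

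**Step 3: the interaction under a constant gap.** Simulation with 3,000 runs, 250 per group, SD 1.995 at each time point, gap 0.3, no program effect and correlations of 0.3, 0.5 and 0.7:

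| Test | Rejection | Bias (serves) |
|---|---|---|
| t test of means at 10 weeks | 37-41% | about 0.30 |
| Difference in change (interaction) | 4-5% | about 0 |
| 10-week value adjusted for baseline value only | 10-25% | 0.09-0.22 |

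The inflation in step 2 therefore belongs to the per-time-point t tests and not to the interaction.

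**Step 4: the interaction when change itself is confounded.** Suppose a factor linked to start date produces a 0.2-serve difference in change with no program effect. With SD 1.995 at each time point, SD of change = 1.995 × √(2(1 − ρ)).

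| ρ | SD of change | k = 0.2 / (SD of change × √(2/250)) | Rejection |
|---|---|---|---|
| 0.3 | 2.361 | 0.95 | 15.7% |
| 0.5 | 1.995 | 1.12 | 20.2% |
| 0.7 | 1.545 | 1.45 | 30.4% |

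The unadjusted interaction does not protect against this.

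**Step 5: what could be adjusted for.** The Participant sampling section of the qualitative study says that the questionnaire captures socio-economic status, age, gender and family structure. No stated test of the program effect uses them.

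**The case against.** The strongest reply is that the plan already contains a difference-in-change analysis. Both primary outcomes are defined as changes, the analysis section says that between-group change will be assessed, it bases the t tests on a split-plot ANOVA, and the sample size uses that ANOVA's interaction. This largely stands. A reader might infer that baseline gaps must pass into the program effect; the documents do not support that, because the t test at 10 weeks is nowhere declared the deciding test. What remains is that the interaction is not declared so either, and that the tests actually named compare means at single time points.

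A reader might also infer a power shortfall, on the ground that the named t test is not the test that was powered. The documents do not support this. A shortfall arises only if the within-person correlation exceeds 0.5; at 0.7 it would need a single-time SD of about 2.57, outside the 1.5 to 2.0 used for the false-positive rates. At SD 1.5 the t test has k = 0.5/0.134 = 3.73 and about 96% power; at SD 2.0, k = 0.5/0.179 = 2.80 and about 80%.

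Nor does the article show that participants picked their own group. It refers to choice of timing, but also to allocated start dates and automated database rules. Allocation is non-random; how far participants determined it is not stated.

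Finally, an article may leave covariate lists to a fuller plan, and sampling bias is disclosed. That is fair for model detail. But the article does state its tests and the purpose of its regression, and neither supplies an adjusted program effect to support the attribution statement.

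**Conclusion.** The point holds in limited form. Every between-group test named is unadjusted, although the groups are non-randomised. The contrast used for sample size is not named as the test of the program effect, and the planned regression is not directed at that effect.

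The false-positive rates of about 9-12% (0.1-serve gap) and 29-46% (0.25-serve gap) apply only to the per-time-point t tests. They assume an SD of 1.5 to 2.0, 250 per group and a two-sided 0.05 test. For the unadjusted interaction the exposure is confounded change: about 16-30% rejection for a 0.2-serve differential change, at an assumed SD of 1.995 and correlation of 0.3 to 0.7. The gaps and the differential change are illustrations; nothing in the article shows that they will occur. The change is worth making because it reduces bias at little cost.

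**What to change.** In the quantitative Data analysis section:

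1. Name the group-by-time contrast from baseline to 10 weeks, already assumed in the Sample size section, as the primary test for both primary outcomes. Controls are surveyed only at these two points.
2. Adjust it for pre-specified baseline covariates that are already collected: age, gender, socio-economic status and family structure. Include each covariate's interaction with time. A covariate main effect alone shifts both time points equally and drops out of the change contrast.
3. Do not substitute adjustment for the baseline outcome alone, which leaves part of a stable group gap in the estimate (step 3).
4. Report the unadjusted contrast as a sensitivity analysis.
5. Label per-time-point and within-group tests as descriptive, with no claim of program effect drawn from them.

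In the Discussion, state that attribution to the program is conditional on the measured covariates.

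The cost is a few degrees of freedom out of a planned 500 participants and slightly more analysis work. No new data collection is needed. Unmeasured confounding, such as motivation linked to start date, would remain and should be stated as a limitation.

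### One split-plot-in-time ANOVA behind the continuous-outcome t tests can give wrong standard errors for the T1-T2 program effect and the T1-T3 change if it is fitted over three unevenly spaced visits

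*Protocol article*

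**What the plan says.** The Data analysis section of the quantitative study opens the comparison with "The magnitude of change both within and between intervention and control groups for T1, T2 and T3 time-points will be assessed". It then names the tests for continuous outcomes: "two sample t tests will be employed to compare means between intervention and control groups at each time point and paired t tests for within". The quote breaks off there; the paired tests compare visits inside each arm. The section adds: "A split-plot in time Anova will be used as the basis for these t-tests".

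The Study design section gives the visits. Intervention participants are surveyed at "program commencement, program completion (10 weeks) and at six months post program completion". For the other arm, "Controls drawn from the waitlist will be surveyed at two time-points", and "A time-three measurement will not be obtained from controls". For vegetable intake alone, "Queensland state-wide monitoring data will be used as a proxy time-three measure for the control group".

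The Sample size section uses the same model name. Its calculation for vegetable intake "assumed the use of a split-plot anova and F test for interaction given the wait list design", with 250 per group for 0.5 serves a day at 80% power and 0.05 significance.

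The article does not say whether the ANOVA takes two visits or three, and it gives no standard deviation, within-person correlation or covariance structure.

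**The concern.** A split-plot in time has one within-person residual. That residual is the right error for each difference between visits only if all those differences have the same variance, which under equal variances means equal correlation between every pair of visits. Here the gaps are about 10 weeks (T1-T2), 26 weeks (T2-T3) and 36 weeks (T1-T3), so equal correlation is doubtful.

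In a three-visit fit, intervention participants supply two residual degrees of freedom each and controls one. The intervention T3 data therefore enter the error used for the T1-T2 group contrast, although T3 adds nothing to that contrast.

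Two results are at stake. The T1-T2 group-by-time contrast is the only one with concurrent study controls, and it could lose power. The T1-T3 change in the intervention group is the direct same-person evidence that a gain over baseline lasts, and it could be declared significant too often.

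**Working it through.** **Inputs from the article.** 250 per group, 0.5 serves, 80% power, 0.05 (Sample size section; the abstract prints 0.5%, which is a separate matter). Visits as in the Study design section.

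**Assumed.** Two-sided test, equal variances σ² at all visits, complete data, and correlations r12, r23, r13 as tabulated.

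**1. The plan's own figure.** The 250 cannot be confirmed because no SD is given. Solving backwards, the SD of T1-T2 change is 0.5 / [(1.960 + 0.842) × √(2/250)] = 1.995. The results below take the stated 80% as the starting point.

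**2. What can be estimated.** Five of the six group-by-visit cells hold study participants. Of the four degrees of freedom between cells, group takes one and time two, so the interaction has one: the T1-T2 contrast. A sphericity correction to an F test does not replace the pooled error used for this one-degree-of-freedom contrast.

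**3. Expected pooled error.** Intervention: 2(n−1) df with expectation σ²(1−r̄), where r̄ is the mean of the three correlations. Controls: (n−1) df with expectation σ²(1−r12). Together:

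MSE/σ² = [2(1−r̄) + (1−r12)] / 3

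**4. Ratio of the pooled to the correct standard error.**

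- T1-T2 group-by-time: k12 = √[(MSE/σ²)/(1−r12)]
- T1-T3 within intervention: k13 = √[(MSE/σ²)/(1−r13)]

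**5. Consequences.** Power at T1-T2 = Φ(2.802 − 1.960·k12). False-positive rate at T1-T3 = 2[1 − Φ(1.960·k13)].

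Example, 0.7/0.5/0.4: r̄ = 0.533; MSE/σ² = (0.933 + 0.300)/3 = 0.411; k12 = √(0.411/0.300) = 1.171; power = Φ(0.507) = 69%; k13 = √(0.411/0.600) = 0.828; false-positive rate = 2[1 − Φ(1.622)] = 10.5%.

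| r12 / r23 / r13 | MSE/σ² | k12 | T1-T2 power | k13 | T1-T3 false positives |
|---|---|---|---|---|---|
| 0.5 / 0.5 / 0.5 | 0.500 | 1.000 | 80% | 1.000 | 5.0% |
| 0.5 / 0.45 / 0.4 | 0.533 | 1.033 | 78% | 0.943 | 6.5% |
| 0.5 / 0.4 / 0.3 | 0.567 | 1.065 | 76% | 0.900 | 7.8% |
| 0.6 / 0.5 / 0.4 | 0.467 | 1.080 | 75% | 0.882 | 8.4% |
| 0.7 / 0.6 / 0.5 | 0.367 | 1.106 | 74% | 0.856 | 9.3% |
| 0.7 / 0.5 / 0.4 | 0.411 | 1.171 | 69% | 0.828 | 10.5% |

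**6. Simulation check** (10,000 runs, 250 per group; patterns 0.5/0.5/0.5, 0.6/0.5/0.4 and 0.7/0.5/0.4). With the pooled error, the T1-T3 false-positive rates were 5.0%, 8.9% and 10.7%, and the T1-T2 rates 4.9%, 3.3% and 2.2%. With each contrast given its own error, the rates were 4.8-5.2% for T1-T2 and 5.1-5.5% for T1-T3.

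**7. Degrees of freedom.** Pooled: 2 × 249 + 249 = 747. T1 and T2 only: 2 × 249 = 498.

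**The case against.** The strongest reply is that the three-visit fit is inferred. The section first names ordinary t tests, and an ordinary paired t test already uses the SD of its own differences. The Sample size section ties the split-plot interaction to the wait-list design, whose shared visits are T1 and T2. A two-group, two-visit split-plot is the same as a t test on individual change and has no such problem. On that reading the T1-T2 half of the point disappears. But a two-visit model cannot be the basis of a paired test involving T3, so the sentence would still not fit the T1, T2 and T3 comparisons it follows.

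It can also be said that covariance structure belongs in an analysis plan that is not shown. That would answer a complaint about missing detail. Here the article names a model, and the named model carries the equal-correlation assumption.

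A reader might infer more than the documents support:

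- **That both standard errors are certainly wrong.** This needs a three-visit fit and correlations that fall with the gap. The article states neither, and equal correlations give no distortion.
- **That every t test is affected.** The sentence covers continuous outcomes only, and two-sample tests at a single visit also involve between-person error, which is not examined here.
- **That the missing control T3 causes the distortion.** It does not; unequal correlation does. What the gap does mean is that the between-group test at each time point has no study controls at T3. The state-wide proxy covers vegetables only and has no individual link to the controls, so it cannot enter the ANOVA.
- **That a false claim of program effect becomes more likely at T1-T2.** Under falling correlation that test is conservative.

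**Conclusion.** The point holds in conditional form. On the natural reading of the Data analysis section, one pooled within-person error serves contrasts whose variances probably differ. Where correlation falls with the gap, the T1-T2 standard error is about 3-17% too large and the T1-T3 standard error about 6-17% too small over the range in the table. That takes power from 80% to about 78-69% and the T1-T3 false-positive rate from 5% to about 6.5-10.5%.

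These figures rest on assumed correlations, equal variances, complete T3 response and a power benchmark taken from the stated sample size. With equal correlations the effect is nil. With complete data only the standard errors are affected, not the point estimates. The T1-T3 change remains an uncontrolled comparison whatever error is used. The wording should be changed, because the remedy costs almost nothing and protects against a plausible departure.

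**What to change.** In the Data analysis section, replace the sentence on the split-plot ANOVA with wording to this effect:

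1. For continuous outcomes, the program effect is the group-by-time contrast fitted on T1 and T2 only, which is equivalent to comparing individual T1-T2 changes between groups.
2. T1-T3 and T2-T3 changes in the intervention group are tested with ordinary paired t tests, each using the SD of its own differences.

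Alternatively, use one mixed model for repeated measures with unstructured covariance and take the group contrast at T2. Either way, say that there is no between-group test against study controls at T3, and that the state-wide vegetable figure is an external comparison outside the model.

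The cost is one or two sentences, with no extra data or participants. The T1-T2 analysis has 498 error degrees of freedom instead of about 747, a negligible loss. The Sample size section rules out any analysis before accrual closes, so the change can be fixed in advance.
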